### Statistical Methods

#### Confirmatory Analysis

A confirmatory analysis with characteristics common for studies designed for the proof of efficacy (two-sided test problem with significance level 5%) is implemented in this Phase II study in order to be able to show superiority of the experimental treatment as compared to the standard treatment in case of a significant result. Confirmatory analysis for the primary endpoint 'time to death for any reason during the follow-up phase of at least 12 months (starting with initial diagnosis)' is based on the full analysis set which is defined according to the intention-to-treat principle and includes all randomized patients. The null-hypothesis of equal survival curves for the two treatment groups is tested by applying the two-sided logrank test stratified by *RPA class. The overall type I error rate is 5%. A g*roup-sequential design is applied with one interim analysis after half of the expected number of events has occurred. The stopping rule is according to [15]: The one-sided critical level in the interim analysis is given by 0.26%, and in the final analysis it is given by 2.4%; the null-hypothesis can be rejected, if the smaller of the two one-sided p-values falls below one of these boundaries. Withdrawals, lost of follow-ups and patients who are still alive by the end of the follow-up phase are treated as censored observations. The censoring date is given by the last known date at which the patient is still alive. The survival curves will be estimated using the Kaplan-Meier product-limit method, and the corresponding confidence intervals will be calculated using Greenwood's formula [19].

#### Descriptive Analyses

To assess the impact of major protocol deviations, an analogous analysis of the primary outcome variable will be performed for the per protocol set of all patients without major protocol violations. A descriptive analysis of the primary outcome variable is performed applying a Cox-regression model including the covariates RPA class, age, Karnofsky index and extent of previous surgery.

Analysis of the secondary endpoint 'progression-free survival' will be performed analogously to the primary endpoint whereby the p-values of the logrank test and the tests within the Cox-regression model will be interpreted descriptively. All further documented variables will be analyzed descriptively by tabulation of the measures of the empirical distributions. Descriptive p-values of the corresponding statistical tests comparing the treatment groups and associated 95% confidence intervals will be given. The homogeneity of the treatment groups will be described by comparison of the demographic data and the baseline values of the measured variables.

Safety analysis and analysis of toxicity will be based on the data set of all randomized patients who were treated with the experimental or the standard treatment at least once. The safety analysis includes calculation and comparison of frequencies and rates of adverse and serious adverse events reported in the two treatment groups.

All analyses will be done using SAS version 9.1 or higher (for the handling of survival analyses with SAS see, [20]).

#### Interim Analysis

To allow for early stopping in case of an overwhelming treatment effect, a group-sequential design is applied with one interim analysis that is performed when 50% of the number of events expected under the null-hypothesis have occurred. Under the assumptions made in sample size calculation, the interim analysis is performed after occurrence of 68 events which should happen approximately 26 months after start of recruitment [18]. The stopping rule is specified according to O'Brien and Fleming (1979; [15]).

No formal boundary for stopping for futility is specified. However, if the results of the interim analysis suggest that the objectives of the study cannot be reached with a feasible number of patients or that the benefit/risk ratio for the study has worsened markedly, the study may be stopped by decision of the principle investigator. As in this case the null-hypothesis would not be rejected, no type I error would be committed and therefore the type I error rate of the study would still be controlled at 5%.

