#### 1. Recruitment period, follow-up duration and allocation ratio

The recruitment period will last 36 months with constant accrual. The minimum follow-up time (for the last patient included in the trial if no event occurs before) will be 12 months, the maximum follow-up time (for the first patient included in the trial if no event occurs before) will be 48 months. Patients will be randomized to the treatment groups with an equal allocation ratio of 1:1.

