#### 2. Overall survival rate

Stupp et al. [2] investigated a study population very similar to the one expected in the CLEOPATRA trial. Hence, according to their results the one-year survival rate for the standard treatment is expected to be about 60%.

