#### 3. Treatment effect size

The CLEOPATRA trial will be designed to detect an improvement of 20% (absolute) in survival rate after 12 months. The rationale behind this assumption is as follows: Carbon ion radiotherapy is characterized by a higher relative biological effectiveness (RBE) as compared to conventional photons or protons. Preclinical experiments on glioblastoma cell lines have shown that this RBE lies between 3 and 5, depending on the respective endpoint or cell line [9]. Therefore, the effect of carbon ion radiotherapy for the treatment of patients with primary glioblastoma is expected to be substantially higher than with conventional proton radiotherapy.

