#### 5. Interim analysis

An interim analysis will be performed according to the stopping rule of O'Brien-Fleming published in 1979 after 50% of the expected events have been occurred [15].

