#### 6. Methods used for sample size calculation

For sample size calculation, exponentially distributed survival times are assumed to calculate the hazard ratio under the alternative. Th*e *formulae proposed by Schoenfeld (which hold true under the less restrictive assumption of proportional hazards) were used [16,17]. Calculations were done using the software ADDPLAN 4.0 [18].

Using the assumptions enumerated above, the resulting total sample size yielding the necessary number of events is 150 patients (75 per treatment group). The expected total number of events under the null-hypothesis is then about 136, under the alternative-hypothesis it amounts to about 115. The total sample size of 150 patients will provide a power of 90,7% to detect a 20% (absolute) improvement in 12 months overall survival rate of the experimental treatment compared to the standard treatment. With this target sample size, CLEOPATRA will also have an adequate power to detect a smaller than anticipated treatment effect (more than 78% power to detect an improvement of 17% (absolute) in 12 months overall survival rate).

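### The interim trigger of 68 events at about month 26 does not follow from the sample-size assumptions; on those inputs 68 events fall at about month 34 (null) or 40 (alternative)

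*Protocol article*

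**What the plan says.** All places are in the protocol article.

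- **Interim Analysis** sets the single look at half of the events expected under the null hypothesis, and states that on the sample-size assumptions "the interim analysis is performed after occurrence of 68 events which should happen approximately 26 months after start of recruitment". The stated purpose is to stop early if the effect is overwhelming.
- **Item 5, Interim analysis** places the look "after 50% of the expected events have been occurred", without naming the hypothesis.
- **Confirmatory Analysis** fixes the boundaries: "The one-sided critical level in the interim analysis is given by 0.26%, and in the final analysis it is given by 2.4" per cent.
- **Items 1 to 3 and 6** give the assumptions. For control, "the one-year survival rate for the standard treatment is expected to be about 60" per cent; the trial is "designed to detect an improvement of 20% (absolute) in survival rate after 12 months"; "exponentially distributed survival times are assumed to calculate the hazard ratio under the alternative"; "The recruitment period will last 36 months with constant accrual"; and "the maximum follow-up time (for the first patient included in the trial if no event occurs before) will be 48 months". The minimum follow-up is 12 months and allocation is 1:1.
- **Item 6** concludes that 150 patients give about 136 events under the null and 115 under the alternative, with 90.7% power. It also claims more than 78% power for a 17-point improvement.
- **Follow-up** ends the trial 12 months after the last patient, about 48 months in all. The final analysis is therefore set by calendar time, not by an event count.

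**The concern.** The event trigger and its date are presented as consequences of the sample-size assumptions, so they can be checked. At month 26, constant accrual has brought in only 150 × 26/36 ≈ 108 patients. Sixty-eight deaths among them would be 63%, although 60% of control patients are assumed to survive a full year and most of the 108 have been followed for less than two years.

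If the date is wrong, the look comes when accrual is nearly or fully complete. The trial team would plan for a decision at month 26 that could still limit the number randomised, and would get one that hardly can. The same look is also the stated occasion for stopping if the objectives have become unreachable or the benefit/risk ratio has worsened, so that review would be late too.

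**Working it through.** **Inputs.** Control survival 0.60 at 12 months (item 2), experimental 0.80 (item 3), exponential curves (item 6), N = 150 at 1:1, uniform accrual over 36 months and analysis at month 48 (items 1 and 6). No dropout rate is given, so I take zero; any dropout lowers the counts and delays the look.

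**Hazards.** λ₀ = −ln(0.60)/12 = 0.04257 per month; λ₁ = −ln(0.80)/12 = 0.01860 per month; hazard ratio = 0.437.

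**The plan's own figure.** 136/2 = 68, so the trigger follows from the stated 136. Against the stated 115 under the alternative it is 68/115 = 59%.

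**Expected events with n patients at hazard λ:**

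- t ≤ 36: E(t) = (n/36)·[t − (1 − e^(−λt))/λ]
- t > 36: E(t) = n − (n/36)·[e^(−λ(t−36)) − e^(−λt)]/λ

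**Month 48.**

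- Null: 150 − 4.1667 × (0.6000 − 0.1296)/0.04257 = 104.0.
- Alternative: 52.0 in control plus 75 − 2.0833 × (0.8000 − 0.4096)/0.01860 = 31.3 in the experimental arm, total 83.2.

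**Month 26.**

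- Null: 4.1667 × [26 − (1 − 0.3306)/0.04257] = 42.8.
- Alternative: 21.4 + 11.2 = 32.6.

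**Solving for the month of the trigger:**

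| | Stated | Null, recomputed | Alternative, recomputed |
|---|---|---|---|
| Events at month 48 | 136 / 115 | 104.0 | 83.2 |
| Events at month 26 | 68 | 42.8 | 32.6 |
| Month of 68 events | about 26 | 34.4 | 40.5 |
| Enrolled at that month | – | about 143 | 150 |
| 68 as share of month-48 events | 50% of 136 | 65% | 82% |
| Month of 52 events (half of 104) | – | 29.2 | 34.1 |

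**What would reproduce the stated figures.** 136 events at month 48 need 12-month survival of about 0.325; 68 events at month 26 need about 0.322. The two agree with each other but not with 0.60. Keeping 0.60, 136 events need about 196 patients, or follow-up to about month 76. Extending the minimum follow-up to 15 months gives only 109.5. Control survival from 50% to 65% moves the null date of the 68th event only between months 30.7 and 36.7.

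**Power.** By Schoenfeld's formula, power = Φ(√d/2 · |ln HR| − 1.96). With d = 115 and HR 0.437 this is about 99%; with d = 83.2 it is about 96.5%. Neither is 90.7%. For 17 points the hazard ratio is 0.512, and 115 events give about 95%, against the claim of more than 78%.

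**Boundaries.** One-sided alpha is 1 − P(Z₁ < z₀.₉₉₇₄, Z₂ < z₀.₉₇₆), with correlation √(information fraction). It is 2.50% at 50%, so the published levels are correct for their design. It is 2.45% at 65% and 2.41% at 82%.

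**Chance of stopping.** Under HR 0.437 the interim boundary is crossed at 68 events with probability Φ(√68/2 × 0.828 − 2.795) ≈ 73%.

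**The case against.** **The interim rule itself is coherent.** The Interim Analysis section names the null hypothesis as the basis, and 68 is exactly half of the stated 136. The less specific wording elsewhere is shorthand, not a contradiction. This stands: the error lies upstream, in item 6, and should be handled together with the event counts and power.

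**The survival rate may be what is misstated.** With 40% versus 60%, exponential curves give about 130 and 117 events, 68 events at month 27.9 (null) or 30.8 (alternative), and power of about 88%. That is nearer the stated outputs, and 68 would be close to half. It is an inference from an approximate match, but it means a reader should not conclude that 60% is right and 136 wrong. The document does not settle which.

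**The exact months depend on the exponential shape.** Item 6 uses that shape to obtain the hazard ratio and notes that its formulae need only proportional hazards. As an illustration of my own, take a Weibull curve through 60% at 12 months and the 14.6-month median quoted in the Background. It gives about 122.5 and 104.6 events, with 68 reached at month 32.2 (134 enrolled) or 36.3 (all enrolled). This softens the figures but does not restore month 26.

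**A reader might infer that the look cannot serve early stopping at all, or that the error rate is compromised.** Neither is supported. The look would still precede month 48 by about 8 to 14 months, with a crossing probability of about 73% under the design effect. The fixed levels become slightly conservative away from 50%, by less than 0.1 percentage point.

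**Conclusion.** The point holds in this form: 68 events at about month 26 is not a consequence of the assumptions it is attributed to. On those assumptions the trigger is about 65% (null) or 82% (alternative) of the expected events, and comes some 8 or 14 months later than stated. What is lost is most of the saving in randomised patients; the chance of an earlier conclusion remains, and type I error is protected. The result rests on exponential survival, uniform accrual and no dropout. That month 26 fails does not depend on fine detail: it survives control rates from 50% to 65% and the Weibull illustration. The source is the set of event counts in item 6, and which of its inputs or outputs is misstated cannot be decided from the document.

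**What to change.** 1. In item 6, reconcile the assumed 12-month survival rates with the stated event counts and both power figures, and say which were used in the software run.
2. Then restate the trigger in the Interim Analysis section as 50% of the corrected count, with its expected date under each hypothesis. If 60%/80% stands, the protocol's null convention gives 52 events, at about month 29 (null) or 34 (alternative). If the rates are revised, the trigger must be derived from the revised count.
3. Optionally, because the final analysis is set by calendar time, evaluate an O'Brien-Fleming-type spending function at the observed information fraction instead of fixing 0.26% and 2.4%. This is a safeguard, not a correction, and could sit in the analysis plan.

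The cost is a recalculation and wording, with no extra patients or visits. One trade-off should be stated: at 52 events and the 0.26% level, the chance of crossing under HR 0.437 is Φ(√52/2 × 0.828 − 2.795) ≈ 58%, against 73% at 68.

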### Data Handling, Storage and Archiving of Date

All findings including clinical and laboratory data will be documented by the investigator or an authorized member of the study team in the subject's medical record and in the CRF. The investigator is responsible for ensuring that all sections of the CRF are completed correctly and that entries can be verified against source data. In some cases, the CRF, or part of the CRF, may also serve as source documents: Karnofsky Performance Status, Documentation of Clinical-Neurological Examination.

Data will be collected by the Study Center at the Department of Radiation Oncology, University Hospital of Heidelberg, Heidelberg, Germany.

After receipt of the CRF-pages by the principal investigator of the study, all data will be entered in a study specific database as recorded in the CRF.

All missing data or inconsistencies will be reported back to the investigators and clarified by the responsible investigator. If no further corrections are to be made in the database it will be declared closed and used for statistical analysis.

The data will be stored and archived according to §13 of the German GCP-Regulation and §28c of the German X-Ray Regulation (RöV) and §87 of the German Radiation Protection Regulation (StrlSchV) for at least 30 years after the trial termination.

### Ethics, informed consent and safety

A positive Ethics Vote was obtained by the Local Ethics Committee of the medical Faculty at the University of Heidelberg, Germany.

Additionally, a positive vote of the Bundesamt für Strahlenschutz (BfS) has been obtained.

### Treatment at tumor progression

After completion of study treatment (5 fractions of proton therapy or 6 fractions of carbon ion radiotherapy according to the treatment arms of the CLEOPATRA trial), adjuvant cycles of chemotherapy with TMZ are recommended in conventional dosing according to the Stupp regimen [2]. Any systemic treatment or chemotherapy is not part of the clinical trial.

For tumor progression, treatment alternatives will be evaluated and discussed interdisciplinary considering options of neurosurgical resection, systemic treatment such as chemotherapy, a second course of radiation therapy, or other.

## Discussion

Interdisciplinary treatment of patients with GBM still remains a challenge in spite of major advances over recent years. The addition of alkylating chemotherapy with the advent of TMZ has significantly increased progression-free and overall survival, however, with a median survival of about 15 months, treatment optimization remains a major challenge [2,21,22]. For more than two decades clinical studies have shown that RT is the single most effective treatment for GBM; however, even after application of high local doses, the majority of recurrences develops within the high-dose irradiation field [23,24]. Therefore, dose-escalation studies have been performed, but increase in dose was mostly related with a steep increase in severe treatment-related side effects.

In contrast to the typical photon dose deposition curve, particle therapy is characterized by a low dose deposition within the entry channel of the particle beam, and the steep dose deposition called the Bragg peak that can be directed by variation of beam energy directly into the defined target volume. Thereafter, a steep dose fall-off helps sparing of normal tissue behind the treatment volume. These physical advantages contribute significantly to the clinical advantage of particle therapy, enabling the radiation oncologist to increase sparing of normal tissue, and subsequently to deliver higher doses to the defined target volume. Carbon ion radiotherapy is additionally characterized by an increased relative biological effectiveness (RBE) due to severe radiation damage produced by the carbon beam. This higher RBE has been shown to translate into improved tumor control rates, especially for treatment-resistant indications.

In the past, particle therapy was only available in few centers worldwide, Today, several institutions offer proton radiotherapy within clinical routine, however, carbon ions are only available in few centers in Japan and Germany. The Department of Radiation Oncology at the University Hospital of Heidelberg is offering carbon ion radiotherapy within clinical routine since 1997. Since then, over 450 patients have been treated successfully with the carbon beam at the Gesellschaft für Schwerionenforschung (GSI) in Darmstadt, Germany. Within the clinical studies performed, excellent clinical results were reported for chordomas and chondrosarcomas of the skull base, high-risk meningiomas as well as adenoid-cystic carcinomas [5,6,25-27]. For several other indications the superiority of particle beams have been demonstrated as summarized by Schulz-Ertner and Tsujii [28].

In Japan, patients with malignant gliomas have been treated with carbon ion beams with convincing results. In a study published by Mizoe et al. patients with anaplastic astrocytomas as well as GBM were treated with photon radiotherapy and a carbon ion boost to the macroscopic tumor. Median overall survival for GBM patients was 17 months, and even the highest doses of carbon ions applied at 24.8 Gy E were tolerated without any severe treatment-related side effects [10]. The increased RBE of carbon ions have been proven by preclinical studies showing an increase in effectivity between 2 and 5, depending on the cell line analyzed [8,9,29]. Today, the standard treatment approach for GBM after neurosurgical resection is combined radiochemotherapy with TMZ as described above [2,22]. *In vitro*, an additive effect of carbon ion radiotherapy and TMZ has been demonstrated [9].

Therefore, In the current Phase II-CLEOPATRA-Study a carbon ion boost will be compared to a proton boost applied to the macroscopic tumor after surgery at primary diagnosis in patients with GBM in combination with after standard radiochemotherapy with TMZ. The study will offer the possibility to compare the carbon ion boost in combination with standard chemotherapy to standard treatment due to the randomized nature of this trial. The aim of the trial is to target the region most likely of tumor recurrence, i.e. the macroscopic region of the tumor within the high-dose irradiation field, and to combine this novel approach with established treatment standards.
